## Abstract

**Background:**

Mental health rehabilitation services provide specialist treatment to people with particularly severe and complex problems. In 2018, the Care Quality Commission reported that over half the 4,400 mental health inpatient rehabilitation beds in England were provided by the independent sector. They raised concerns that the length of stay and cost of independent sector care was double that of the NHS and that their services tended to be provided much further from people’s homes. However, there has been no research comparing the two sectors and we therefore do not know if these concerns are justified. The ACER Study (Assessing the Clinical and cost-Effectiveness of inpatient mental health Rehabilitation services provided by the NHS and independent sector) is a national programme of research in England, funded from 2021 to 2026, that aims to investigate differences in inpatient mental health rehabilitation provided by the NHS and independent sector in terms of: patient characteristics; service quality; patient, carer and staff experiences; clinical and cost effectiveness.

**Methods:**

ACER comprises a:1) detailed survey of NHS and independent sector inpatient mental health rehabilitation services across England; 2) qualitative investigation of patient, family, staff and commissioners’ experiences of the two sectors; 3) cohort study comparing clinical outcomes in the two sectors over 18 months; 4) comprehensive national comparison of inpatient service use in the two sectors, using instrumental variable analysis of routinely collected healthcare data over 18 months; 5) health economic evaluation of the relative cost-effectiveness of the two sectors. In Components 3 and 4, our primary outcome is ‘successful rehabilitation’ defined as a) being discharged from the inpatient rehabilitation unit without readmission and b) inpatient service use over the 18 months.

**Discussion:**

The ACER study will deliver the first empirical comparison of the clinical and cost-effectiveness of NHS and independent sector inpatient mental health rehabilitation services.

**Trial registration:**

ISRCTN17381762 retrospectively registered.

## Background

Most people diagnosed with a severe mental illness such as schizophrenia recover at least partially, but around 25% develop longer term, complex problems that require mental health rehabilitation services [1, 2]. These include persistent, severe ‘positive’ symptoms (delusions and hallucinations) and ‘negative’ symptoms (reduced motivation, verbal communication and emotional reactivity), alongside poor organisational skills due to specific cognitive impairments associated with the illness. Recovery is often further complicated by substance misuse and co-morbid physical health problems (such as obesity, diabetes, cardiovascular and pulmonary disease). Some people also have pre-existing conditions such as intellectual impairment and/or developmental disorders, including those on the autism spectrum. These multiple problems impact negatively on the person’s social and everyday functioning (self-care, housework, shopping, cooking, budgeting and interpersonal skills) and may lead to challenging behaviours [3]. Many will struggle to engage in community activities or gain employment, and over half are vulnerable to self-neglect and exploitation [4, 5]. In short, without appropriate treatment and support, quality of life for people with complex psychosis is poor.

Due to their complexity, admissions to inpatient rehabilitation services are longer than general (‘acute’) mental health admissions and community support costs for this group are high; it has been estimated that around half the total health and social care budget for mental health is spent on people with complex psychosis [6]. Nevertheless, our previous research has shown that with access to local NHS rehabilitation services, most people can gain the skills to manage with less support over time, graduating from inpatient care to higher, and then lower, supported accommodation [7, 8]. However, recent years have seen major disinvestment in NHS inpatient mental health rehabilitation services across England and increasing reliance on the independent sector.

In 2018, the Care Quality Commission (CQC) surveyed all providers of inpatient mental health rehabilitation services in England [9]. They reported the cost of inpatient rehabilitation to be over £500 m per year, with the independent sector providing around half the 4,400 beds in the country. They noted that use of the independent sector varied greatly by Clinical Commissioning Group (CCG) and admissions to independent sector rehabilitation units were twice as long as those at NHS units. Although the cost per day was similar, admissions to the independent sector therefore cost twice as much. The CQC also found that patients treated in the independent sector were much further from home than those receiving NHS care and they raised concerns about the social dislocation this caused for patients. They highlighted a lack of evidence-based rehabilitation being provided in many units and questioned whether the current system represented an appropriate use of public funds, stating ‘Too often, these…rehabilitation hospitals are in fact long stay wards that institutionalise patients, rather than a step on the road back to a more independent life in the person’s home community.’

The CQC report [9] attracted considerable negative press [10, 11] and prompted a national initiative by NHS England (‘Getting It Right First Time’– GIRFT) to encourage Clinical Commissioning Groups (CCGs) to invest in local NHS mental health rehabilitation services [12]. The recently published NICE Guideline on mental health rehabilitation modelled the potential cost savings if all inpatient rehabilitation were to be provided by the NHS and estimated this at £52,000 per patient (an estimated total saving of over £100 m per year) [13]. However, this may be overly optimistic since there have been no studies comparing the quality and outcomes of NHS and independent sector providers of rehabilitation. A reversal of the current system risks wasting the expertise gained by the independent sector and major investment may be required to rebuild NHS services. Furthermore, there may be bias in the CQC data since NHS Trusts may be transferring patients with higher complex needs to the independent sector, necessitating longer admissions [14, 15].

The Assessing the Clinical and cost-Effectiveness of inpatient mental health Rehabilitation services provided by the NHS and independent sector (ACER) study will be the first to compare the clinical and cost effectiveness of NHS and independent sector inpatient mental health rehabilitation services. Our findings will be of obvious relevance to those who require these services and their families, and will help inform commissioners and policy makers about the most appropriate use of resources for this complex group.

### Aim and research questions

Our overarching aim is to investigate the clinical and cost-effectiveness of inpatient mental health rehabilitation provided by the NHS and independent sector with the objective of investigating differences between them in terms of: patient characteristics; service quality; patient, carer and staff experiences; clinical effectiveness; and their relative cost effectiveness.

Our specific research questions are:

Do sociodemographic and clinical characteristics of patients differ between people receiving inpatient rehabilitation in the NHS and the independent sector?Does service quality differ between inpatient rehabilitation units provided by the NHS and the independent sector?Do the experiences of treatment and care, from the perspectives of patients, informal carers and staff, differ between inpatient rehabilitation services provided by the NHS and the independent sector?Is inpatient rehabilitation clinically more effective at preventing readmission when provided by the independent sector or the NHS, after adjusting for differences between the sectors in terms of patient characteristics and length of stay?Is inpatient rehabilitation more cost effective when provided by the independent sector or the NHS, after adjusting for differences between the sectors in terms of key predictors of costs such as patient characteristics and length of stay?

## Methods

### Design

The ACER study is comprised of five Components:

a survey of NHS and independent sector inpatient mental health rehabilitation services across England to compare the quality of services and patient characteristics in the two sectors.a qualitative investigation of patient, family, staff and service commissioners’ experiences and perspectives on inpatient mental health rehabilitation provided by the two sectors.a cohort study comparing successful rehabilitation in the two sectors for the patients recruited in Component 1.a service evaluation retrospectively comparing successful rehabilitation over an 18-month period in the two sectors for all users of inpatient rehabilitation services in England on a specific census date, using instrumental variable analysis of routinely collected healthcare record data.a health economic evaluation calculating the relative cost effectiveness of inpatient rehabilitation services provided by the NHS and the independent sector using data from Components 1, 3 and 4.

### Project management

The sponsor for the ACER study is Camden and Islington NHS Foundation Trust.

#### The North London Service User Research Forum (SURF)

SURF will be consulted throughout the study at four separate points on aspects of the project including any necessary substantial amendments to the study design, interpretation of findings and dissemination.

#### Project management organisation

Figure 1 shows how the different groups described above relate to each other and provides an overview of how the project management is organised.

**Fig. 1 Fig1:**
[figure not shown]
Project management organisation

#### Local approvals

NHS Trusts and independent sector providers of eligible services will be approached by the research team about potential participation in the study. The research team will work together with organisations who agree to take part in this study to put in place all the necessary local approvals.

### Component 1: survey of NHS and independent sector inpatient mental health rehabilitation services in England

Component 1 (C1) addresses research questions 1 and 2.

Do sociodemographic and clinical characteristics of patients differ between people receiving inpatient rehabilitation in the NHS and the independent sector?Does service quality differ between inpatient rehabilitation units provided by the NHS and the independent sector?

#### Scoping of inpatient mental health rehabilitations services

We will first contact all NHS Mental Health Trusts and our local collaborators at our independent sector provider partners to identify potentially eligible inpatient rehabilitation services for the study. In terms of the independent sector, we have agreements in place with Priory Group and St Andrew’s Healthcare, for their eligible services to be available for selection in this study. We will confirm details of the number and types of inpatient rehabilitation units provided and use the typology of inpatient rehabilitation services developed by the Royal College of Psychiatrists [16] to categorise units. We will also collect information about their location (urban, suburban, rural), size (number of beds) and gender mix (mixed or single sex). We aim to recruit similar numbers of different unit types in both sectors and will consider the need for stratified random sampling (by provider, unit type, size, location etc.) once the initial scoping is completed.

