#### Service eligibility criteria

Only high dependency, community, or longer term high dependency rehabilitation units are eligible for the study. Community rehabilitation units will only be included if they are registered with CQC as an inpatient unit (rather than supported housing or residential care). We will exclude highly specialist units that focus on sub-groups (such as people with a diagnosis on the autism spectrum or those with neurodegenerative disease). We will also exclude specialist forensic mental health units (i.e. low secure rehabilitation units) as they do not form part of the standard mental health rehabilitation care pathway and are subject to specialist commissioning by NHS England. We will consider excluding very small units (fewer than 10 beds) to ensure adequate patient recruitment and an average cluster size of 8, in keeping with the number of patients per unit recruited in the Rehabilitation Effectiveness and Activities for Life (REAL) study, a previous national programme of research in NHS inpatient rehabilitation services led by the Chief Investigator [4, 7].

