#### Analysis

The data analysis for C1 will be primarily descriptive, reporting the characteristics of the participants and the participating services in the two sectors.

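### Component 1 balances unit types across sectors and states no step back to each sector's real unit mix, so research questions 1 and 2 lose the part of any sector difference that comes from unit mix

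*Protocol article*

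**What the plan says.** Component 1 is assigned research questions 1 and 2. The first is: "Do sociodemographic and clinical characteristics of patients differ between people receiving inpatient rehabilitation in the NHS and the independent sector". The second asks the same about service quality. Neither carries a condition. Research questions 4 and 5, in the section on aim and research questions, do: they ask for a comparison after adjustment for differences between the sectors.

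Three unit types are eligible: "Only high dependency, community, or longer term high dependency rehabilitation units are eligible for the study". For selecting units, the scoping section says "We aim to recruit similar numbers of different unit types in both sectors", and that the team "will consider the need for stratified random sampling (by provider, unit type, size, location etc.) once the initial scoping is completed". The same section says of scoping: "We will confirm details of the number and types of inpatient rehabilitation units provided". Location, bed numbers and gender mix are also recorded.

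On the NHS side all mental health trusts are contacted. On the independent side contact is with partner providers, and two named groups have agreed "for their eligible services to be available for selection in this study".

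The Component 1 analysis is a single sentence. It is "primarily descriptive, reporting the characteristics of the participants and the participating services in the two sectors". It does not mention weighting, standardisation or results by unit type. The sample of 500 (250 per sector) also serves Component 3, and its size was taken from the Component 3 power calculation.

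**The concern.** The unit types are distinguished by dependency and expected length of stay, so patient characteristics, and service features such as the proportion detained or average stay, may well vary between them. If the two sectors provide these types in different proportions, that mix is one route by which their patients and services differ. Recruiting similar numbers of each type from both sectors closes that route by design.

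This suits Component 3, which wants comparable groups. It fits less well with questions about the sectors as they are. The Background raises the possibility that NHS trusts transfer people with more complex needs to the independent sector. If some of that transfer takes the form of a different unit mix, a type-balanced description would not show that part, and a reader could take the smaller gap as the sector difference.

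**Working it through.** **The plan's own figure.** The only number attached to Component 1 is its size. With d = 0.38, two-sided 5% and 90% power, a two-sample t test needs 146.5, so 147 per group, or 294. Then 294 × 1.19 = 349.86, so 350, and 350 × [1 + (8 − 1) × 0.06] = 350 × 1.42 = 497. The figure reproduces. It does not bear on this point, which concerns what the sample represents.

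**Decomposition.** Let w(N,k) and w(I,k) be the true shares of unit type k in the NHS and the independent sector, p(N,k) and p(I,k) the prevalence of a characteristic in that type and sector, and b(k) the common share of type k in a balanced sample.

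- Sector difference as it is: Σ w(I,k) p(I,k) − Σ w(N,k) p(N,k).
- Difference in a balanced, unweighted sample: Σ b(k) [p(I,k) − p(N,k)].

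The second keeps the within-type differences. What it drops depends on how far the true shares depart from b(k).

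**Illustration. All inputs are assumed, because the documents give neither unit mix nor prevalence by type.** There are two types, A and B, with 70% and 30% prevalence in the NHS. The balanced sample is half A and half B in each sector; because the within-type gap is constant, any common split gives the same balanced result.

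No sector difference within type:

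- Type A share 40% NHS, 60% independent: NHS 0.4 × 0.7 + 0.6 × 0.3 = 0.46; independent 0.6 × 0.7 + 0.4 × 0.3 = 0.54; true gap 8 points, balanced 0.
- 30% and 70%: 0.42 and 0.58; true gap 16 points, balanced 0.
- 20% and 80%: 0.38 and 0.62; true gap 24 points, balanced 0.

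Independent sector 10 points higher within each type (80% and 40%):

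- The same three mixes give true gaps of 18, 26 and 34 points; the balanced sample shows 10 in each.
- With the mix reversed (60% NHS, 40% independent): NHS 0.6 × 0.7 + 0.4 × 0.3 = 0.54; independent 0.4 × 0.8 + 0.6 × 0.4 = 0.56; true gap 2 points, balanced 10. The balanced figure is therefore not always the smaller one.

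**When nothing is lost.**

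- Mix 50/50 in both sectors: true 10, balanced 10.
- Prevalence the same in both types (50% NHS, 60% independent) at any mix: true 10, balanced 10.
- If the two sectors share a mix that differs from the sample's, the two figures still agree as long as the within-type gap is the same in every type.

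**Price of weighting back.** With equal variance in both types (here 0.7 × 0.3 = 0.3 × 0.7 = 0.21) and the same clustering, the variance of a sector's weighted estimate relative to its balanced one is Σ w(k)²/b(k).

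- Shares 40/60: (0.16 + 0.36)/0.5 = 1.04, so intervals about 2% wider (√1.04 = 1.02).
- Shares 30/70: (0.09 + 0.49)/0.5 = 1.16, about 8% wider (√1.16 = 1.08).
- Shares 20/80: (0.04 + 0.64)/0.5 = 1.36, about 17% wider (√1.36 = 1.17).

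**Can another component fill the gap?** Component 4 covers every user of inpatient rehabilitation in England on its census date, with no balancing by type. Its variable list has age, gender, ethnicity, HoNOS items, admission dates and service use. It has neither unit type nor QuIRC data, so it cannot answer research question 2 and addresses research question 1 on only a few variables.

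**The case against.** A reader might infer that Component 1 removes the sector differences altogether, so that the sectors would look alike because the sample was built that way. The documents do not support this. Units are balanced by type but patients are not matched: everyone in a participating unit is eligible unless on leave or without enough English to consent. If the independent sector takes more complex patients into the same type of unit, Component 1 will show it.

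A reader might also infer that the plan commits to an unweighted description. It does not say so. The analysis sentence is silent, and an article may leave weighting to an analysis plan that is not shown. Balance is also an aim and not a quota, with stratified sampling still undecided.

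For research question 2, comparing quality between like unit types is a defensible headline, since a mix-weighted QuIRC score blends provider quality with the kind of service commissioned. One sample has to serve two components, which makes comparability a reasonable priority. Any illustrated size rests on assumed inputs.

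All of this stands, and it limits the point without removing it. The sampling aim is stated and changes what the stated questions measure, and the article does not say whether they concern the sectors as they are or like-for-like units.

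**Conclusion.** The point holds in a limited form. Carried out as written, the balancing aim takes out of the comparisons for research questions 1 and 2 the part of any sector difference that is due to unit mix, and nothing stated in the article puts it back. Within-type differences are kept.

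The size is unknown. Under the assumed inputs the sector-level gap is misstated by 8 to 24 points, in either direction. It is not misstated where the sectors' mixes are equal and the within-type gap is constant, or where the characteristic does not vary by unit type. The sample size and the Component 3 comparison are unaffected. This is a moderate to minor matter of design and reporting. It is worth correcting because Component 1 is the component assigned to research questions 1 and 2, and the information needed is already being collected.

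**What to change.** - Keep the balanced sampling of units for Component 3.
- State in the Component 1 analysis whether each of research questions 1 and 2 concerns the sectors as they are or like-for-like units.
- Report Component 1 results by unit type within sector.
- For the sector-level answer to research question 1, add estimates that weight each unit type to its share of beds in that sector's sampling frame, as counted at scoping. For research question 2, give the same weighted estimates beside the like-for-like comparison.
- Label the unweighted table as a comparison at equal unit mix.
- Word independent-sector conclusions as applying to the participating providers. Weighting to the partner providers' beds does not extend them further.

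The cost is a little more analysis and somewhat wider intervals from unequal weights (about 2% to 17% under the assumed mixes). No new data are needed, since scoping already records the number, type and size of units. A type present in a sector's frame but with no participating unit cannot be weighted, and should be reported as not covered.

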#### Service eligibility criteria

Only high dependency, community, or longer term high dependency rehabilitation units are eligible for the study. Community rehabilitation units will only be included if they are registered with CQC as an inpatient unit (rather than supported housing or residential care). We will exclude highly specialist units that focus on sub-groups (such as people with a diagnosis on the autism spectrum or those with neurodegenerative disease). We will also exclude specialist forensic mental health units (i.e. low secure rehabilitation units) as they do not form part of the standard mental health rehabilitation care pathway and are subject to specialist commissioning by NHS England. We will consider excluding very small units (fewer than 10 beds) to ensure adequate patient recruitment and an average cluster size of 8, in keeping with the number of patients per unit recruited in the Rehabilitation Effectiveness and Activities for Life (REAL) study, a previous national programme of research in NHS inpatient rehabilitation services led by the Chief Investigator [4, 7].

#### Patient eligibility criteria

All patients of inpatient rehabilitation units that are participating in the study will be eligible for participation, with the exception of those on leave (with or without formal permission) at the time of recruitment (this comprised 8% of patients in the REAL study [4]) and those who lack adequate English to give informed consent (1% in the REAL study [4]). The vast majority of patients at these units have a diagnosis of schizophrenia or bipolar affective disorder (89% in the REAL study [4]).

We will include patients in C1 who are assessed as lacking capacity. We expect only a minority of eligible patients to lack capacity (around 8% based on the REAL study [4]) but it is important they are included in the study in order to prevent sample bias [4].

